## Abstract

The United Nations, through its 2030 Agenda and Sustainable Development Goals, advocates for the establishment of conducive environments for physical activity, following the ecological model. In line with this initiative, active transportation emerges as an accessible, cost-effective, and sustainable approach to augmenting daily physical activity levels. This study protocol endeavors to assess the impact of an active transportation education program rooted in the ecological model on the physical and mental well-being of high school students. Drawing upon scientific insights, we hypothesize that a 16-week active transportation intervention will lead to a 3% reduction in average body fat percentage and a noteworthy enhancement in executive function (including inhibition, cognitive flexibility, and working memory), physical fitness (comprising cardiorespiratory fitness and muscle strength), and mental health (encompassing mood disorders and cognitive functioning). If this intervention proves effective, it could offer a viable solution for the school community, especially in reducing congestion within the school environment. The study protocol aims to evaluate the impact of an active transportation educational program based on the ecological model on the physical and mental well-being of high school students. Three high schools located in the urban area of Talca, Chile, will be randomly selected (one public, one privately subsidized, and one private non-subsidized). Each high school will be randomly assigned an experimental group (n = 30) and a control group (n = 30; without intervention). The experimental groups will receive an active transportation educational intervention during their physical education classes for four months (60 to 90 min sessions, once a week), while the control group will receive no intervention. The primary outcome will provide information on body composition and executive function. Secondary outcomes will include objective physical activity level, physical fitness, mental well-being, academic achievement, health-related quality of life, perception of environmental urban features, physical activity barriers, and adherence to active transportation. It is expected that the results of the MOV-ES Project will transcend the physical health of schoolchildren and will have an impact on the school community, especially by decongesting the school environment.

## 1. Introduction

Physical inactivity is the fourth most important risk factor for mortality worldwide, and it is responsible for the deaths of five million people per year, making it a global public health priority [1,2]. Approximately 80% of adolescents fail to meet international physical activity recommendations, which state that ≥60 min of moderate to vigorous physical activity should be performed every day [3]. Given this problem, the World Health Organization (WHO), through the “Global Action Plan on Physical Activity 2018–2030”, proposes to reduce physical inactivity worldwide by 10% by 2025 and 15% by 2030 through initiatives to promote physical activity that involve a systemic view of the problem and that consider the school system as a relevant actor [4].

The importance of promoting physical activity at school age lies in the fact that it is in childhood and adolescence where the learning of healthy lifestyles, habits, and good living should be learned and strengthened [5,6,7], especially in adolescence (high school), as studies show that physical activity decreases during this phase [8,9]. Sustained physical inactivity behaviors lead to increased overweight/obesity in the school population [10,11], and mental health problems [12]. It is estimated that the cost associated with physical inactivity and obesity in Chile amounts to USD 103 million per year, with a direct cost of USD 69.2 million, of which 31.7% is borne by the family [13].

The WHO points out that one of the reasons for the low physical activity level at school age is the school itself, due to the long days of low energy expenditure within the school [14]. There is evidence that the times when there is most physical activity in school are before school (transportation), during recess, lunch, and after school [15]. In this overall scenario of physical inactivity, active transportation (walking or cycling to and from school) represents an opportunity for children to engage in regular physical activity [16], becoming an economical and sustainable option that impacts the daily living of schoolchildren [17,18,19,20,21]. A meta-analysis indicates that active transportation could contribute between 23% and 36% of daily physical activity in children and adolescents [22]. Other studies show that schoolchildren who walk or cycle to school achieve higher levels of physical activity [23], lower adiposity [20,24], better cardiorespiratory fitness [25], a higher level of happiness and well-being [26], and improved academic achievement [27] compared to schoolchildren who do not use it.

The rate of active transport use among schoolchildren varies from country to country [9], but in general, it is low and is steadily declining in more economically developed countries [28,29,30,31]. In Chile, there is a lack of studies to establish an objective rate of Chilean schoolchildren who use active transportation to school [32], which is evidenced in the latest Notebook (Global Matrix Chile) [11]. The incipient evidence indicates that only 8.9% of schoolchildren engage in active transportation [32], which is very different from the data presented by a Chilean government agency, where 18.1% of adolescents report daily active transportation [33]. However, both data are lower than those reported in cities such as Ottawa (35.5%), Bogotá (72.14%), Helsinki (81.1%), Cape Town (51.3%), and Baton Rouge (10.8%) [34]. These differences in percentages should be understood based on the country’s characteristics, which should be equivalent to the level of economic development and the need versus choice that people have to opt for active or motorized transport [35]. Some systematic reviews identify predictors of transportation in children, highlighting demographic characteristics, individual and family, school, and physical and social environmental factors [36,37]. Other studies have focused on parental barriers to active transportation, establishing a negative and significant association between traffic and personal safety within the neighborhood adjacent to the school [38]. A recent study affirms that parents’ perceptions of active transportation differ according to the distance of the home from the school [39]. In this context, the greater the distance, the lower the levels of social support, the greater the environmental barriers, and the greater the safety concerns regarding physical activity, walking to school, and, less consistently, bicycling to school [39].

Recent studies in the Chilean school population have analyzed the impact of various physical activity interventions [40,41,42]. However, active transportation interventions in the Chilean school population have not been explored. The evidence indicates that interventions that involve a socio-ecological view of the problem, including intrapersonal factors (biological and motivational), interpersonal (social) and community networks, and socioeconomic, cultural, and environmental conditions, benefit the student and their environment [43,44,45]. In this sense, the ecological model proposed by Sallis et al. indicates that active living behaviors are determined by the influence of intrapersonal, interpersonal, and physical environment factors, which specifically influence four domains of active living: occupation, transportation, domestic activities, and recreation [46]. By intervening in each of these, community physical activity levels can be increased. However, studies that establish objective data on physical activity and active transportation in Chile are lacking.

The effectiveness of active transportation interventions in the school setting has been widely studied [20,21,24,34]. The benefits of this type of intervention do not only include increased physical activity in schoolchildren but also increased positive emotions during the school trip [47], increased safety in the city [48], and improved academic achievement [49]. There is also evidence that promoting this type of transportation has an impact on the community [50,51], especially in the reduction in traffic congestion, exhaust, and greenhouse gas emissions [52,53,54]. Furthermore, although there are studies on active transportation in the Chilean population [32,33,55,56,57,58,59], there is a need for further studies focused on the school population.

At an international level, the work carried out at the University of Otago (New Zealand), through its BEATS Research program, stands out [50,60,61]. It is an interdisciplinary and multidisciplinary study based on the relationship between parents, academia, community, and government. Its purpose is to analyze the individual, social, environmental, and political influences on adolescents’ active transportation (walking or cycling) to school [60]. Within the project, some sub-studies yield cross-sectional [60] and longitudinal [50] data that support the proposal of the present study. In New York City, the Safe Routes to School program was implemented, increasing the rate of active transportation in the city and even reducing congestion and pollution [62]. In Spain, the University of Granada developed the “Pedalea y Anda al Cole (PACO)” project, which collected cross-sectional data on active transportation in different Spanish cities [63] and analyzed the effect of an educational intervention on active transportation to school by bicycle [64]. The PACO and PACA projects are currently being implemented; like the PACO Project, the intervention is educational and focuses on the use of bicycles [65].

Regarding the intervention duration, there is no consensus on how many weeks or months are best to increase physical activity through active transportation [64]. There are programs that intervene for one or two years [66,67], four months [68], or just a few weeks [69]. Most of the evidence that monitors and intervenes in the active transportation variable belongs to works from the United States of America [66,69,70], Spain [63,64], Denmark [71], the United Kingdom [72], Canada [67], Australia [73], and New Zealand [19]. However, there are no longitudinal studies in Latin America, which is relevant considering the differences with developed countries in terms of the school entry system, especially in Chile, where the variable “proximity to the home” may not be a determinant in the choice of the educational establishment [74].

From the call made by experts to design strategies contextualized to the local reality of active transportation to school [75,76] to increase physical activity levels and improve the physical and mental health of children, the project “Moving to School” (MOV-ES) was born. This project will be carried out during the period 2024–2026 in a city in Southern Chile that has urban characteristics below the national average in terms of population density (949.8 inhabitants/km^2^), sports facilities (0.81 m^2^/inhabitant), green areas (6.40 m^2^/inhabitant), and pollution problems above the national average [77]. Therefore, the aim of this study protocol for the MOV-ES project is to determine the effect of an active transport educational program based on the ecological model on the physical and mental health of high school students. Given the evidence from previous studies focused on reducing physical inactivity, it is hypothesized that (i) the MOV-ES intervention will result in a 3% decrease in mean percent body fat in the experimental group compared to the control group, and (ii) the MOV-ES intervention will result in a significant increase in executive function (inhibition, cognitive flexibility, and working memory), physical fitness (aerobic capacity and muscle strength), and mental health (mood disorders, cognitive functioning) in high school students.

## 2. Material and Methods

### 2.1. Study Design

This study includes an experimental design (randomized controlled trial), double blind, repeated measures, two parallel groups (one intervention and one control), and a quantitative approach. The methodology followed will be the Consolidated Standards of Reporting Trials Statement (CONSORT) methodology [78]. Figure 1 summarizes the study’s design.

### 2.2. Ethical Approval

The protocol of the current study adheres to the principles outlined in the updated Declaration of Helsinki and has received approval from the Human Ethics Committee of the Universidad Católica del Maule, Chile (approval number: N°27/2024). Prior to participation, all participants will provide written informed assent, and their parents will provide consent. Furthermore, the study has been registered in the Clinical Trial Protocol Registry and Results System (ClinicalTrials.gov) of the United States of America (code: NCT06357065; link: https://classic.clinicaltrials.gov/ct2/show/NCT06357065?cond=active+transport&draw=2&rank=1, accessed on 26 April 2024).

### 2.3. Sample Size Calculation

While feasibility trial results typically inform sample size calculations for scalability cluster randomized trials, an approximate sample size estimate is required for budgeting this large-scale trial. The sample size was determined to be 3 clusters (classrooms) per condition (n = 6 clusters) using the GRT sample size calculator from the NIH (researchmethodsresources.nih.gov). This calculation considered an absolute difference of 3% (alpha error of 0.05 and statistical power of 0.80) between the experimental group (EG) and control group (CG) in mean body fat percentage (with a standard deviation of 5), an average of 30 participants in each cluster, and a variance inflation factor of 1.05 based on prior research findings. Following the feasibility study and informed by qualitative research insights, adjustments will be made to refine the MOV-ES intervention.

### 2.4. Randomization and Blinding

All schools in the city of Talca, Chile, are electronically randomized to select three high schools located in the urban area of Talca (1 public, 1 private subsidized, and 1 private unsubsidized). Each high school will have an EG (n = 30) and a CG (n = 30; no intervention). This selection approach is in line with the Chilean educational system, which associates school administration with the socioeconomic level of families.

### 2.5. Participants

All first-year high school students (approximately aged 15 to 16 years old) from the chosen schools will be invited to participate in this study. Inclusion criteria for the students entail: (i) enrollment in the designated school; (ii) parental or legal guardian authorization (consent); (iii) do not have any motor problems to perform autonomous transport; and (iv) voluntary agreement from the students to take part in the study (assent).

### 2.6. Intervention

The CG will participate in the initial and final measurements but will not receive any intervention, attending their traditional physical education classes. On the other hand, the EG (MOV-ES) will receive an educational intervention within their physical education class. The contents of this intervention involve intrapersonal (benefits of active transportation and safety on the way to school), interpersonal (family safety), organizational, community, physical-environmental, and political (safety, infrastructure, and quality) factors [79]. The program will comprise a weekly session lasting 60 to 90 min each, spanning a total of 16 weeks. The entire intervention program was conducted during school hours within the framework of physical education classes and hosted on the premises of each respective institution. The curriculum will be structured into didactic units, which are divided into 16 subtopics that will be addressed in each of the sessions. Each session will have the following structure: (i) audiovisual presentation; (ii) application of content; and (iii) practical work. The contents will be complemented by the presentation of graphic and audiovisual materials together with practical components in the school space.The contents will follow the recommendations for active transportation interventions in schoolchildren [75] and the material available from the PACO Project (http://profith.ugr.es/pages/investigacion/recursos/manualbici, accessed on 20 June 2024). A summary of the progression and unit structure of the MOV-ES interventions is presented in Table 1.

The sessions of the last month of intervention will include practical activities in bicycle mechanics and walking in the school environment (outside the school). Depending on the possibilities of each school, cycling sessions will be included. At the end of the intervention, and to motivate students to engage in active transportation, both EG and CG participants will receive educational infographics.

### 2.7. Outcomes and Procedures

The research team has established partnerships with municipal corporations as well as public and private institutions through collaborative agreements. The project’s work plan will be consistently upheld throughout each year of its execution. At the beginning of each year, the randomization of establishments will take place. The research team will establish communication with the educational institutions, where they will introduce the study’s aims, duration, and key aspects of the data collection process to teachers and school administrators. Measurement days will be coordinated during this interaction. To inform and obtain consent from parents, the research team will employ various communication strategies: (i) request the school management unit to disseminate information about the study through available channels (e.g., emails, websites, notice boards); and (ii) arrange either virtual or in-person meetings with parents of each class (parent-teacher meetings), during which researchers will address inquiries about the research process and invite parents to complete the parental questionnaire. Informational materials about the study will be provided to the school for parents who do not have email access or could not attend the informational session. Parents will have the option to provide consent either in writing or electronically (recorded). Upon obtaining parental consent, student measurements will be scheduled. A battery of questionnaires and physical tests, based on the ecological model of physical activity and active transportation, will be administered, covering intrapersonal, interpersonal, organizational, community, physical-environmental, and political dimensions (pre- and post-intervention).

All the assessments will be carried out during the physical education class time, either in the classroom or at the designated location for each class. The research team will inform students about the project’s aims using informational materials; upon obtaining their assent, students will receive a kit containing an informational document about the study, the battery of school questionnaires, and the parental informed consent form. For this purpose, the research team will bring all the available material. It is estimated that the application of the questionnaire and the anthropometric measurements will last 3 h for each class measured (2 physical education class sessions).

#### 2.7.1. Primary Outcomes

The primary variables and the selected instruments for their measurement are summarized in Table 2. In addition to sociodemographic variables (such as birth date and gender), the following information will be collected from each participant at baseline:

Body composition: The percentage of fat mass and fat-free mass will be obtained using eight electrodes of tetrapolar bioimpedance (InBody 570^®^, Body Composition Analyzers, Seoul, Republic of Korea). Prior to the assessments, students will be asked to come to the measurement in light clothing, without metal-containing garments, and with the possibility of removing their footwear. This whole process will be carried out under the supervision of a school teacher.

Executive function: The NIH Toolbox for Assessment of Neurological and Behavioral Function^®^ (NIH Toolbox^®^ in Spanish, v. 1.8) was created as a comprehensive set of neurobehavioral assessments intended to rapidly evaluate sensory, motor, emotional, and cognitive abilities throughout the lifespan, spanning ages 3 to 85 years, available in both English and Spanish [80]. Inhibitory control and attention will be measured using the Flaker Test of Attention and Inhibitory Control. Cognitive flexibility and attention will be measured using the Dimensional Change Card Sorting Test, and working memory will be measured using the List Sorting Working Memory Test. For each test, the evaluator will read the specific instructions of the test to be applied, making sure, by verbal confirmation, that the subject understands the procedure. The results of the tests are extracted by means of scores.

#### 2.7.2. Secondary Outcomes

Anthropometric measurement: the following measurements are included: (i) body mass in kilograms using a digital scale (Seca 769, Hamburg, Germany; Accuracy of 0.1 kg); (ii) standing height in centimeters measured with a stadiometer (Seca 220, Hamburg, Germany; Accuracy of 0.1 cm); (iii) six diameters (biacromial, transverse thorax, anteroposterior thorax, bi-iliocrestid, humeral, femoral) in centimeters using an anthropometer (Rosscraft Campbell 20, Richmond, BC, Canada; Accuracy of 0.1 mm); (iv) ten circumferences (head, relaxed arm, arm under tension, maximum forearm, mesosternal thorax, minimum waist, maximum hip, maximum thigh, medial thigh, maximum calf) in centimeters measured with an inextensible measuring tape (Seca 201, Hamburg, Germany; Accuracy of 0.1 cm); and (v) six skin-fold thicknesses (triceps, subscapular, supraspinal, abdominal, medial thigh, calf) in millimeters assessed using a caliper (Harpenden, Hitchin, UK; Accuracy of 0.2 mm). According to the International Society for the Advancement of Kinanthropometry (ISAK) [81], all assessments will be performed by an ISAK level II anthropometrist.

Physical activity level (objective): Measurement of objective physical activity level will be by Actigraph Accelerometer—Model wGT3X-BT, Pensacola, FL, USA. They include a microelectromechanical system (MEMS)-based accelerometer, ambient light, and a touch sensor as data collection endpoints. The study subjects will wear the device for 6 full days [82]. At the end of the measurement period, the accelerometer will be removed by the technical staff of the research team for analysis. Sedentary time will be set at <1100 count/minute, light intensity between 1100 and 3200 count/minute, and moderate-vigorous intensity at >3200 count/minute. Accelerometry data will be valid if they present ≥3 days of measurement with a minimum of 9 h of use per day. The data obtained through the accelerometers will be further processed by the Actilife 6.13.4 software and the GGIR statistical package [83].

Physical fitness: It will be assessed with the application of different tests validated in the school population, with high reliability and ease of application. The order of application of the tests contemplated is: (i) A 20 m shuttle run test will be used to measure the maximal oxygen consumption (VO_2_ max). This test allows a very reliable and easy-to-use evaluation. This is a maximal test involving a continuous run between two lines separated by 20 m at the same time as the beeps are recorded [84]. The athlete’s score is the level and number of laps (20 m) achieved before he/she could not keep up with the recording. (ii) A long jump test with feet together will be used to measure lower body muscle strength [85]. This test allows for or assesses the explosive force (power) of the extensor muscles of the legs; the number of centimeters advanced, from the jump line to the edge closest to the jump line, of the foot that was farthest behind after the fall is recorded. (iii) The upper body muscle strength will be assessed with the hydraulic dynamometer (Camry, model EH101, Zhongshan, China), which allows evaluation of great reliability and easy application [86].

Mental well-being: This will be measured with the Depression, Anxiety, and Stress Scale (DASS-21). Is an instrument designed to assess the negative emotional states of depression, anxiety, and stress [87,88]. The depression subscale is formed by questions 3, 5, 10, 13, 16, 17, and 21. Questions 2, 4, 7, 9, 15, 19, and 20 formed the anxiety subscale. The stress subscale was formed by questions 1, 6, 8, 11, 12, 14, and 18. The total scores categorize each subscale into three levels: mild, moderate, and severe. Finally, participants will be classified as no risk (<6) or risk (>6).

Academic achievement: To assess this variable, the grades of all subjects from the first academic semester will be considered and compared with those of the second semester (intervention). The rating scale in Chile is from 1 to 7, with 7 being the maximum rating.

Health-related Quality of Life: An instrument that measures the health-related quality of life of adolescents. It is a self-report instrument applicable to healthy and chronically ill children and adolescents aged 8 to 18 years [89]. The KIDSCREEN-27 measures five dimensions: physical well-being (5 items), psychological well-being (7 items), autonomy and parents’ relations (7 items), peers and social support (4 items), and school environment (4 items) (Cronbach’s alpha = 0.89).

Perception of environmental urban features: Neighborhood Environment Walkability Scale (NEWS). A self-report measure that has recently been developed to assess perceived neighborhood environmental attributes related to physical activity. The full version was designed and validated among North American youth. Subsequently, it was translated into other languages and has been used in Spain [90,91]. It is composed of items that collect information on residential density, access to services, connectivity, walking and cycling infrastructure, neighborhood aesthetics, neighborhood safety, and access to sports facilities.

Physical activity barrier: The short scale of perception of physical activity barriers in adolescents will be used [92]. It consists of 12 questions that collect the self-perception of the different items included in the scale. Each item will be evaluated using a 5-point Likert response scale, where 1 means strongly disagree and 5 means strongly agree (Cronbach’s alpha = 0.80).

Active Transportation: A questionnaire that includes questions on reasons for choosing a particular school, transportation habits to school, motivations and barriers to walking and bicycling to school, perceived neighborhood environment, health behaviors, perceptions of driving, and use of information and communication technology. This questionnaire is based on the PACO Project [93].

Physical activity level (subjective): This will be assessed using the Physical Activity Questionnaire for Adolescents (PAQ-A) [94]. It consists of nine questions that evaluate different aspects of physical activity performed by adolescents in the previous 7 days, using a 5-point Likert scale for each question. It reports information on the intensity, frequency, and duration of each activity performed. The overall result gives a score from 1 to 5, where a higher score indicates a higher physical activity level. Participants will complete the Spanish version (ICC = 0.71).

School questionnaire: Based on the questionnaire used in the Spanish ALADINO study [95]. It includes date of birth, sex, place of residence, sports experience, grade, date and time of measurement, clothes worn at the time of measurement, and name and address of the school.

Parents’ self-perceived physical fitness: using the International Fitness Scale (IFIS) questionnaire [96]. It has a Spanish version, and there are studies published in Chile that use it [97]. This questionnaire is composed of five Likert-type questions that describe the perception of general fitness, cardiorespiratory fitness, muscle strength, speed agility, and flexibility (Kappa = 0.45).

Parents’ Physical Activity Level: Global Physical Activity Questionnaire (GPAQ) designed by WHO. It incorporates information on physical activity participation and sedentary behavior in three settings: activity at work, activity while moving, activity during leisure time, and activity at work [98].

Cultural, social, and political context: School Questionnaire (Directors): Includes questions related to school physical activity policy, infrastructure, sports equipment, educational mission and vision, food received at school, and access to food during school hours.

Covariates: familial socioeconomic status, perception of environmental urban features parent’s and physical fitness parent’s.

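### The fitness battery opens with a maximal run, so the long jump that follows may carry leg fatigue; putting the run last is a free improvement

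*Protocol article*

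**What the plan says.** The Physical fitness paragraph of section 2.7.2 (protocol article) lists three numbered tests and states that the numbering is the sequence of use: "The order of application of the tests contemplated is: (i) A 20 m shuttle run test". On the run it adds "This is a maximal test involving a continuous run between two lines separated by 20 m", scored by the level and laps "achieved before he/she could not keep up with the recording". The second test reads "ii) A long jump test with feet together will be used to measure lower body muscle strength", and the article explains that it "assesses the explosive force (power) of the extensor muscles of the legs". The third reads "iii) The upper body muscle strength will be assessed with the hydraulic dynamometer".

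Section 2.7 sets the place and time: "All the assessments will be carried out during the physical education class time". It also estimates 3 h per class over 2 lessons, but for the questionnaire and anthropometry only. For the fitness tests the article gives no duration, allocation to lessons or rest interval.

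Hypothesis (ii) in the Introduction predicts a significant increase in "physical fitness (aerobic capacity and muscle strength", among other outcomes. Section 2.8.1 adjusts the models for baseline value, age and classroom.

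**The concern.** By the article's own description, a run continued to the student's limit comes immediately before a test of explosive force in the legs. This is a declared sequence, so a field manual that followed it would inherit the problem. Two things are at stake for the jump.

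- **Noise.** Students drop out of a shuttle run at different times. Unless rest is controlled, the interval before the jump can differ between students and between visits, and the jump score then includes a recovery-dependent component.
- **Possible distortion of the arm comparison.** Hypothesis (ii) expects gains in both running and strength. If the EG runs further than the CG at the final visit and is more tired as a result, its jump is held down and a true strength gain is partly masked. Adjusting for the baseline jump cannot remove a carry-over that changes between visits in one arm only.

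**Working it through.** The article gives no figure for the fitness tests, so there is none to reproduce. Its one computed design figure, 3 classrooms per condition, concerns body fat percentage and plays no part here.

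**Model.** Let the observed jump equal the fatigue-free jump minus k times the running result, where

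- k = fatigue-free jump SDs lost per SD of extra running (assumed 0.1 to 0.3);
- D = EG minus CG difference in running at the final visit, in SD (assumed 0.2 to 0.5 in favour of the EG).

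Neither input is in the documents. The loss common to both arms cancels, so

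bias in the EG-CG jump contrast = -k × D.

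| k | D = 0 | D = 0.2 | D = 0.3 | D = 0.5 |
|---|---|---|---|---|
| 0 | 0 | 0 | 0 | 0 |
| 0.1 | 0 | -0.02 | -0.03 | -0.05 |
| 0.2 | 0 | -0.04 | -0.06 | -0.10 |
| 0.3 | 0 | -0.06 | -0.09 | -0.15 |

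The non-zero entries run from -(0.1 × 0.2) = -0.02 to -(0.3 × 0.5) = -0.15 SD.

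**Does baseline adjustment remove it?** This was simulated with 400,000 students per scenario, a true strength effect of zero, the same test order at both visits, and regression of the final jump on arm and baseline jump. The simulation has no classroom clustering, so it checks bias and says nothing about precision.

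| k | D | Estimated arm effect (true value 0) |
|---|---|---|
| 0 | 0 | 0.001 |
| 0 | 0.3 | 0.001 |
| 0.2 | 0 | 0.003 |
| 0.2 | 0.3 | -0.058 |

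With a residual SD of at most 1, the simulation standard error is at most 2/√400,000 = 0.003. The first three rows are therefore compatible with zero, and the last with the formula value of -0.2 × 0.3 = -0.06. Baseline adjustment leaves the distortion in place when k and D are both non-zero, and there is none when either is zero.

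**Noise.** If residual fatigue varies between students independently of their true jump, its variance adds to that of the jump score in both arms. The documents give nothing from which to size this.

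**The case against.** The strongest reply is that harm to the arm comparison needs several conditions together: tests close in time, incomplete recovery, fatigue that depends on the run, and arms that differ in running at the final visit. The documents establish none of them, and hypothesis (ii) only predicts the last. Only one order is stated, so on its face it applies to both arms and both visits, and a shared loss cancels. The programme is one weekly educational session, with months 1 and 2 in the classroom (Table 1), so a marked running gain is not assured. Rest intervals are a detail that an article may leave to the full protocol.

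Most of this stands, and it rules out several stronger readings.

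- A reader might infer that students reach the jump tired in proportion to how far they ran. The article does not say so. A maximal test takes each student to a personal limit, and fitter students may recover faster, so k could be near zero or even negative, which would reverse the direction.
- A reader might infer that the strength outcomes are biased as a matter of course. The zero cells in the table show otherwise.
- A reader might express the harm in centimetres. An assumed loss of 3% to 8% on an assumed 150 cm jump is 4.5 to 12 cm, but that is an individual's whole loss, largely common to both arms, and not a between-arm bias.
- A reader might include grip strength. The argument is about tired legs, and carry-over to the hand is doubtful.
- A reader might extend the point to bioimpedance or the NIH Toolbox tests. The article states no order for those relative to the fitness tests.

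The objection does not dispose of the sequence itself. It is stated explicitly, it puts exhaustive leg work before a leg-power test, and no reason for it is given.

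**Conclusion.** The point holds as a weakness in measurement procedure, confined to one secondary outcome. If the tests are close together, the long jump may carry recovery-dependent noise. It may also carry a small arm bias of about -0.02 to -0.15 SD, provided that k lies between 0.1 and 0.3 and the EG outruns the CG by 0.2 to 0.5 SD. Both ranges are assumptions. The bias is zero if the arms run equally far or recovery is complete. Body composition, executive function and the sample size are untouched. This is a free improvement and does not threaten the trial's main conclusions.

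**What to change.** Before baseline testing begins, change the order in section 2.7.2 to hand grip, then standing long jump, then the 20 m shuttle run last, and state that it applies in both arms and at both visits. The change should not be made between a cohort's baseline and final measurements, because that would break the pre-post comparison.

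Adding the same-visit running result to the model is not a substitute: at the final visit it is itself an outcome that the programme may affect.

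The cost is an edit to the protocol and the field manual. Tests, staff and testing time stay the same.
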